### Follow-up and end-points

At 6-month follow-up, participants will be contacted by telephone or email to undergo similar testing as baseline, except vascular imaging. The primary endpoint will be changes from baseline Fuster BEWAT score (FBS) which has shown a strong inverse association with subclinical atherosclerosis (24). FBS will enable the monitoring of global changes in healthy behaviors and non-laboratory-based CV health factors. The FBS measures CV risk exclusively on the basis of the easily measurable predictors blood pressure [B], exercise [E], weight [W], alimentation [A], and tobacco smoking [T], and is thus a highly relevant outcome given the characteristics of our study population. Secondary outcomes will include changes in overall knowledge, attitudes, and physical activity, diet, smoking, cholesterol, glucose, blood pressure, weight, and self-rated family health. We expected that women who underwent imaging will improve their CV lifestyle in a better way than women who do not undergo imaging because they will be witnesses of their own vascular damage, and thus, the FBS will score higher in the imaging group. Similar procedures will be carried out on the 12-month visit to evaluate long-term effects. CV events will be also registered in all follow up visitsfor participants with plaques, and also for those without plaques, as well as data regarding the approach taken by the participant inquiring whether she has any new medical treatment, has seen a healthcare professional with her results or if additional testing has been ordered based on blood tests or vascular imaging results.

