*Z_α_*_/2_ and *Z_β_* are the critical values for the chosen significance level and power (splitting the significance level evenly between tails); *p*1 is the proportion of individuals who develop the disease without treatment, 45% according to the PESA study. *p*2 is the proportion of individuals who develop the disease with treatment, assuming 54% of our individuals will follow the provided recommendations to reduce the CVFR probability. With this setup, *n* = 481 patients will report a statistical power 1−*β* of 80% and significance level *α* of 95%, which are satisfactory in terms of clinical purposes. Given our previous experience with lifestyle intervention programs, we are well powered to detect relevant changes in the imaging group. Larger effects are anticipated in individuals with plaques, as there is more room for improvement. To account for potential variability introduced by including women across a wide age range, we will stratify participants into predefined age groups (e.g., young: 40–50 years: adult: 50–60 years, elderly: 60–70 years) during analysis. Additionally, we will apply multivariable regression models adjusted for age as a continuous variable to control for age-related confounding factors. This approach ensures that the impact of age on the progression of the atherosclerotic process is appropriately considered and mitigates the risk of contamination of information between age groups.

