Noninvasive imaging allows the detection of early atherosclerosis, which improves risk reclassification and independently predicts CV events. The clinical significance of early atherosclerosis has been established in several large population-based studies, including MESA, HRP, Rotterdam and CAFES-CAVE studies (33–37). These studies showed that the presence of plaque, even in asymptomatic phases, was associated with CV events in long-term follow-up and improved risk reclassification, highlighting the importance of imaging early atherosclerosis (38). In the PESA study (39), which included >4,000 asymptomatic individuals, imaging was used to study multiterritorial subclinical atherosclerosis creating the basis for the inclusion in the latest European Guidelines of VUS imaging for atherosclerosis screening in low to moderate risk asymptomatic individuals (38). Vascular ultrasound imaging provides visual evidence of an individual's arterial health status and, more importantly, presence of plaque; this is especially attractive for raising awareness of the importance of CV disease in women and encouraging appropriate lifestyle changes. There are several trials that have explored the impact of visualization of coronary calcium score findings on the improvement of patient adherence to preventive care. Rozanski et al. compared the clinical impact of conventional risk factor modification to that associated with the addition of coronary artery calcium scanning finding that calcium scanning was associated with superior coronary artery disease risk factor control and improvement of patient adherence to preventive care (40). Another example of the effect of visualizing coronary calcium on improvement of statin treatment adherence was described by Kalia NK et al. (41). Event prediction with VUS is comparable to coronary calcium score, while avoiding harmful exposure to ionizing radiation, an especially important consideration for young women. Further advantages of VUS include the technique's portability, low cost, innocuous profile and potential improvement over population-based risk scales. We will use 2DVUS for plaque detection as well as 3DVUS, to assess atherosclerotic plaque burden with the added advantage of volumetric quantification. We also plan to develop a novel VUS application for vessel-wall tracking based on strain-rate techniques to assess early vascular mechanics changes specifically in women with RFs or subclinical disease. This technique will allow us to assess arterial stiffness, which is a surrogate of structural and functional changes within arterial walls and a potential marker of target-organ damage. Several validated ultrasound-based techniques and arterial stiffness parameters are available; however, all of them have technical limitations regarding acquisition, measurement and interpretation (32, 42) which have precluded their clinical implementation. Hence, there is a clear need for improved methods. According to previous studies, a 12-month period seems to be insufficient to observe notable changes in plaque dimensions and thus, VUS has not been included at follow up. WAKE UP will provide a one-of-a-kind dataset unavailable from any other study and will likely set the basis for future research directions, including a long-term follow-up for assessing subclinical atherosclerosis progression or regression as a result of lifestyle improvement and eventually, CV events in a female-specific cohort.

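### The sample size is not defined on the primary endpoint: it compares proportions developing disease, with an adherence rate as p2, so the stated 80% power does not apply to the FBS

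*Protocol article*

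**What the plan says.** Follow-up and end-points (Protocol article) fixes the outcome: "The primary endpoint will be changes from baseline Fuster BEWAT score (FBS"). The imaging group is expected to score higher. Changes in knowledge, attitudes, individual behaviours and risk factors are secondary. Cardiovascular events are registered at the follow-up visits but are listed neither as primary nor as secondary.

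Statistical analysis says that the FBS will be analysed by multivariate logistic regression, with improvement or worsening between baseline and follow-up as the dependent variable. It then prints a formula for comparing two proportions. Of its inputs, p1 "is the proportion of individuals who develop the disease without treatment, 45% according to the PESA study", and p2 "is the proportion of individuals who develop the disease with treatment, assuming 54% of our individuals will follow the provided recommendations". The critical values are two-sided ("splitting the significance level evenly between tails"). The result is that "481 patients will report a statistical power" "of 80% and significance level" "of 95%, which are satisfactory in terms of clinical purposes". The section does not say whether 481 is per arm or in total.

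Study design and population plans 720 women randomised 1:1, 360 per arm, with ultrasound at baseline only and only in the imaging arm. The Discussion gives the reason: "a 12-month period seems to be insufficient to observe notable changes in plaque dimensions and thus, VUS has not been included at follow up".

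**The concern.** The calculation and the endpoint concern different things. The calculation uses the proportion who develop disease with and without treatment, which is not an endpoint of this trial. The inputs also do not fit each other. One is a disease proportion and the other is the share of women expected to follow advice, so the 9-point gap between them is not a treatment effect on anything. Its direction is also opposite to the hypothesis, because as defined the disease rises from 45% to 54% with treatment.

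At stake is the only quantitative justification for the size of the trial. No FBS mean, SD, target difference or proportion improving appears in the document, so a null FBS result could not be read against any effect that the trial was designed to detect.

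**Working it through.** **Inputs.** From Statistical analysis: p1 = 0.45; p2 = 0.54; two-sided test; power 80%. The significance level is printed as 95% and is read here as α = 0.05. From Study design and population: 360 per arm.

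**1. Reproduce the plan's figure.** The printed formula is

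n = (Z_α/2 + Z_β)² · [p1(1−p1) + p2(1−p2)] / (p1−p2)²

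- (1.9600 + 0.8416)² = 7.8489
- 0.45·0.55 + 0.54·0.46 = 0.2475 + 0.2484 = 0.4959
- (0.45 − 0.54)² = 0.0081
- n = 7.8489 · 0.4959 / 0.0081 = 480.5, rounded up to **481**

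The arithmetic is right. This formula gives the number per arm, so the total is 2 · 481 = 962.

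**2. Was 54% really entered as p2?** Two other readings were tried in the same formula:

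| Reading of p2 | p2 | n per arm |
|---|---|---|
| 54% entered directly | 0.54 | 481 |
| 9-point reduction from 45% | 0.36 | 464 |
| Complement of 54% | 0.46 | 38,923 |

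Only the direct entry gives 481. The adherence figure was used as the treated disease rate.

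**3. Can the outcome in the calculation be observed?** New atherosclerosis would need imaging at follow-up in both arms. Ultrasound is done once, in one arm. Cardiovascular events are recorded, but 45% is not a plausible 12-month event proportion in asymptomatic women without prior cardiovascular disease. It is closer to the atherosclerosis prevalence of nearly 50% that the Introduction gives for women aged 40–54.

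**4. The most favourable reading.** Suppose that 45% and 54% are relabelled as the proportions whose FBS improves. With 360 per arm:

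- SE = √(0.4959/360) = 0.03711
- 0.09/0.03711 = 2.425
- Power = Φ(2.425 − 1.960) = Φ(0.465) = **0.679**

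A pooled-variance version gives 0.676. Power is about 68% before loss. If 481 were read as a total, about 240 per arm, power would be about 51%.

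**5. What 360 per arm delivers on a binary FBS outcome.** Assume that 45% of controls improve. Solving the printed formula for p2 at 80% power and two-sided 5%:

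- 360 per arm: p2 ≈ **55.4%**, a difference of about 10.4 points
- 288 per arm (20% loss, assumed; 360 · 0.8): p2 ≈ **56.6%**, a difference of about 11.6 points

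**6. What it delivers on mean FBS change**, if the primary analysis were changed to that form. The detectable difference is √(2 · 7.8489/n) in units of the SD of the change score:

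| n per arm | SD units | Points if SD = 1.5 | SD = 2 | SD = 2.5 | SD = 3 |
|---|---|---|---|---|---|
| 360 | 0.21 | 0.31 | 0.42 | 0.52 | 0.63 |
| 288 | 0.23 | 0.35 | 0.47 | 0.58 | 0.70 |

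The SD range is an assumption; the document gives none.

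**The case against.** The strongest reply is that the form of the calculation suits the analysis. The FBS is to be analysed as improvement or worsening, which is binary, so a two-proportion formula is reasonable. On this view, disease is loose wording carried over from a textbook definition; the sentence on p2 goes on to speak of lowering risk-factor probability. This stands in part. A reader might infer that using proportions for a 15-point score is itself the error, and the documents do not support that. The fault lies in how p1 and p2 are defined and where they come from. Better wording alone would not repair it, because no source is given for either figure as a proportion improving, and on that reading 360 per arm falls short of the plan's own 481.

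The reversed direction matters little numerically: a 9-point fall needs 464 per arm instead of 481. It is an error of definition, not of size.

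A reader might also infer that the trial measures no disease at all. That is too strong, because cardiovascular events are registered at follow-up. They are simply not an endpoint.

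Finally, the article says that experience with earlier lifestyle programmes, and studies using the FBS, make the trial adequately powered. That claim is qualitative and gives no effect size, SD or response rate, so it cannot stand in for the calculation.

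**Conclusion.** The point holds. The stated 80% power relates to an outcome that is not an endpoint, uses an adherence rate as a disease rate, and carries no information about the FBS. Neither 481 nor 720 is justified by it.

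On the most favourable relabelling, the requirement is 481 per arm (962 in total) against 360 planned, with about 68% power before loss. That figure depends wholly on taking 45% and 54% as proportions improving, which the document does not say. A reader might therefore infer that the trial is shown to be underpowered for its primary endpoint. It is not: without FBS inputs, its power for the FBS is unknown, and 360 per arm may be adequate for a difference worth detecting. What has to be corrected is the justification.

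**What to change.** Replace the disease-proportion paragraph with one that uses the same form of the endpoint as the planned analysis.

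- **Matching the planned logistic regression:** define p1 and p2 as the proportions whose FBS improves in the control and imaging arms, with a source, and state n per arm and in total. Possible wording: *With 360 women per arm and a two-sided 5% significance level, the trial has 80% power to detect FBS improvement in 55.4% of the imaging arm v 45% of controls, or 56.6% v 45% if 20% are lost.* The 45% and the 20% are placeholders until sourced. Say why a difference of that size is worth detecting.
- **If the primary analysis is changed to mean FBS change:** state that 360 per arm detects 0.21 SD of the change score (0.23 SD with 20% loss), say which SD is meant, give points over an SD range, and amend the logistic regression text to match.

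In either case, print the significance level as 5%. The cost is one rewritten paragraph and a search for FBS response rates or SDs. Enrolment stays at 720 if the detectable difference is judged acceptable. If the sponsor wants 80% power for 45% v 54% improving, 720 is too few, and the target difference or the sample size has to be reconsidered.

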## Methods

### Study design and population

WAKE UP is a longitudinal, prospective, case-control study that will include 720 women aged 40–70 years-old (from pre- to post-menopause) with at least one CV RF, defined as cigarette smoking, hypertension, dyslipidaemia, diabetes, obesity, poor diet, physical inactivity, family history of premature CV disease, metabolic syndrome, systemic autoimmune collagen-vascular disease, history of premature menopause, gestational diabetes or hypertensive disorders of pregnancy according to prevention guidelines for women (17). Exclusion criteria include any prior history of CV disease (myocardial infarction, angina pectoris, arrythmias, stroke, peripheral vascular disease, angioplasty, valvular heart disease, congenital heart disease or heart surgery), pregnancy and refusal to sign informed consent.

The study will include baseline, 6-month and 12-month follow-up visits (Figure 1). All visits will include traditional and non-traditional risk assessment, blood sampling and omics analysis (Table 1). Vascular imaging studies will be only performed at baseline, after randomization 1:1 for imaging risk assessment, 360 with VUS vs. 360 age- and RF-matched controls without imaging. Participants in the imaging group will be informed about their personalized CV risk based on imaging results and will be given lifestyle recommendations accordingly. Women with atherosclerotic plaque will be shown their arterial images and will be explained the meaning and CV risk associated with these findings. Those without plaques will be shown example images of atherosclerotic plaque and similar explanations will be given.

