### Statistical analysis

Preliminary descriptive statistical analysis (boxplots, histograms, univariate parametric and non-parametric tests) will be used once significant amounts of data have been collected. All parameters to be collected are summarized in Table 2. We will evaluate lifestyle changes by the FBS using multivariate logistic regression. The dependent variable will be the improvement or worsening of the score between baseline and follow-up, and the analysis will be adjusted for covariates such as age to identify groups of women potentially more impacted by the imaging-based strategy. Additionally, machine learning techniques will be derived to acquire knowledge from the data. In particular, supervised and semi-supervised classifiers will be trained with 80% of the data to derive risk prediction models. Remaining 20% of the data will serve as a validation cohort. Also, clustering analysis will be performed in order to observe phenotype groups in our patients that explain the clinical variance for sample size calculation, the following formula was applied:$$n=\frac{{\left(Z_{\alpha /2}+Z_{\beta }\right)}^{2}\cdot (\;p_{1}\cdot (1-p_{1})+p_{2}\cdot (1-p_{2}))}{{\left(\;p_{1}-p_{2}\right)}^{2}}$$

**Table 2 T2:** WAKE UP study variables.

Questionnaires	
- CV risk perception	health problems, personal health conditions, CV risk and general knowledge regarding CV disease in women
- CV risk factors	smoking, hypertension, dyslipidaemia, diabetes, obesity, poor diet, physical inactivity, family history CVD, metabolic syndrome, systemic autoimmune collagen-vascular disease, preeclampsia or gestational diabetes
- Non-CV disease	Thyroid disorders, chronic renal failure, pulmonary disease, hepatic disease, cancer, autoimmune disease
- CV risk scores	FBS, SCORE, SCORE 2, ASCV, FHS 10, FHS 30
- Smoking	Age of initiation, n° of cigarettes per day, exposure to secondary smoking
- Physical activity	Hours sitting on a workday, time spent walking on a workday, practice of moderate and/or intense exercise
- Diet	Portions of carbohydrates, proteins, fruits and vegetables, dairy products, sweets, fat, water and alcohol
-Reproductive factors	Age of menarche, contraceptive use and type, complications during pregnancy, age of menopause
-Psychosocial factors	Education level, employment status, marital status, stress scale, emotional state scale

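### The sample-size formula's 481 is a per-group number (962 in total); the planned 360 per arm gives about 68% power on the article's own inputs, not 80%

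*Protocol article*

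**What the plan says.** In the protocol article, Statistical analysis, the authors write that "for sample size calculation, the following formula was applied" and print the two-proportion expression n = (Zα/2 + Zβ)² · [p1(1 − p1) + p2(1 − p2)] / (p1 − p2)². The text after Table 2 gives the inputs:

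- For p1 the value is 0.45, described as "the proportion of individuals who develop the disease without treatment, 45% according to the PESA study".
- For p2 the value used is 0.54, with the explanation "assuming 54% of our individuals will follow the provided recommendations".
- The test is two-sided, since the critical values are described as "splitting the significance level evenly between tails".
- The conclusion drawn is that "481 patients will report a statistical power"; the power is given as 80%, and alpha is printed as 95%.

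The number 481 is not labelled as per group or total. The next sentence, appealing to earlier experience with lifestyle programmes, adds that "we are well powered to detect relevant changes in the imaging group".

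The planned size is stated in the Abstract and under Study design and population: 720 women randomised 1:1, "360 with VUS vs. 360 age- and RF-matched controls without imaging". The article gives no other sample-size calculation and no allowance for loss to follow-up.

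**The concern.** Read without a label, 481 patients against 720 planned looks like a surplus of 239 women. If the formula gives a per-group number, the comparison is instead 962 needed against 720 planned, a shortfall of 242. The only quantitative justification of the trial's size would then show the reverse of what a reader takes from it.

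The stake is how a null result is read. A reader who believes the trial had at least 80% power would take no difference as fair evidence against imaging. On the article's own assumptions, the chance of missing the assumed difference is about one in three, before any loss over the 12 months.

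Two details in the same paragraph add to the problem. A significance level of 95% is a confidence level written in place of alpha. And the assurance about power speaks of change in the imaging group, whereas the hypothesis and the stated expectation for the primary endpoint are that the imaging group does better than the group without imaging.

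**Working it through.** **Inputs** (all from Statistical analysis, except the arm size, which is from Study design and population): p1 = 0.45; p2 = 0.54; power 80%, so Zβ = 0.84162; alpha 5% split between tails, so Zα/2 = 1.95996; 360 women per arm.

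**1. Reproduce 481.**
- (1.95996 + 0.84162)² = 7.8489
- 0.45 × 0.55 + 0.54 × 0.46 = 0.2475 + 0.2484 = 0.4959
- (0.54 − 0.45)² = 0.0081
- n = 7.8489 × 0.4959 / 0.0081 = 480.5, rounded up to 481

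The article's figure is reproduced, which also confirms that alpha was 5%.

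**2. Per group or total?** With n women in each arm, the variance of the difference in proportions is [p1(1 − p1) + p2(1 − p2)] / n. Setting 0.09 equal to (Zα/2 + Zβ) times its square root and solving for n gives the printed formula. So n is the size of each arm, and the total is 2 × 481 = 962.

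**3. Is p2 really 0.54?** The text is ambiguous, because 54% is described as an adherence share. Other readings do not return 481: p2 = 0.45 × 0.46 = 0.207 gives 55 per group, and p2 = 0.45 × 0.54 = 0.243 gives 80. Using 0.54 directly reproduces the number.

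**4. Power at the planned size.** Power = Φ(0.09 / √(0.4959 / m) − 1.96), with m per arm. For m = 360: √(0.4959 / 360) = 0.03711; 0.09 / 0.03711 = 2.425; Φ(2.425 − 1.96) = Φ(0.465) = 0.679.

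| Women per arm | Basis | Power, two-sided 5% |
|---|---|---|
| 481 | formula's requirement | 80.0% |
| 360 | planned | 67.9% |
| 324 | 10% loss (assumed) | 63.3% |
| 306 | 15% loss (assumed) | 60.9% |
| 288 | 20% loss (assumed) | 58.3% |
| about 240 | if 481 were the total | 51% |

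The loss rates are assumptions, since the article gives none. With a pooled null variance, power at 360 per arm is 67.6%, and the requirement for 80% is 484 per group.

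**5. Difference detectable with 80% power at 360 per arm.** Solving the formula for p2 with n = 360 and p1 = 0.45 gives p2 = 0.554, a difference of 10.4 points. Check: 0.45 × 0.55 + 0.554 × 0.446 = 0.4946; √(7.8489 × 0.4946 / 360) = 0.104.

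**6. Would a one-sided test rescue it?** The article splits alpha between tails, so this is not its plan. A one-sided 5% test would need 379 per group, still above 360, and would have 78% power at 360.

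**The case against.** The arithmetic is not in dispute. The case on the other side concerns what may be concluded from it.

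- **The 80% is attached to 481, not to 720.** This is correct as a matter of wording: no sentence says that 360 per arm has 80% power. But no other calculation supports 720, and the paragraph moves straight from 481 to an assurance of adequate power. The plan's requirement and its arm size still disagree by 121 per arm.
- **The 68% is not the power for the primary endpoint.** This stands as a limit on the figure. The primary endpoint is change in FBS, analysed as improvement or worsening, while the calculation defines p1 and p2 as proportions developing disease, takes p2 from an adherence share, and sets it above p1. Power for FBS cannot be derived from the article. That is a separate weakness, and it does not make 481 a total or 360 per arm sufficient.
- **The assurance about power rests on earlier experience and could mean change relative to controls.** That reading is possible. Literally, though, it names the imaging group only, and no figure supports it on either reading.
- **Stratified randomisation and covariate adjustment may alter power.** They may, but the article gives nothing from which to quantify a gain, and its own calculation is unadjusted.
- **The 95% is a slip of notation.** Agreed. It does not affect the numbers, but it should be corrected in the same edit.

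**Conclusion.** The concern holds. By the article's own formula and inputs, 481 is the number per group, so 962 women are needed for 80% power at 45% versus 54%. The planned 360 per arm gives about 68% (67.9% unpooled, 67.6% pooled), or 80% power for a difference of 10.4 points, before any loss to follow-up. Reading 481 as a total does not help, because 481 women in all would give about 51%.

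The result assumes a two-sided 5% test, an unadjusted comparison of two proportions and complete follow-up. It is conditional on the stated 45% and 54% and says nothing directly about power for FBS. It needs correction because the sole justification of the trial's size is misreported in the direction that flatters the design.

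**What to change.** Keep 720 women and correct the sample-size paragraph:

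1. State that 481 per group (962 in total) would be needed for 80% power at 45% versus 54%, two-sided alpha 5%.
2. State that 360 per group gives about 68% power for that difference, or 80% power for a 10.4-point difference (45% versus 55.4%), before loss to follow-up.
3. Replace the 95% significance level with a two-sided 5%.
4. Delete the assurance about power in the imaging group, or replace it with the between-arm figure from item 2.
5. Say in the same sentence what the two proportions measure, so that the restated power is not taken for power on FBS.

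The cost is wording only: no extra participants and no change to any procedure. The stated power becomes less favourable. Reaching 80% for the 9-point difference would instead take 242 more women (962 − 720), before any allowance for loss; the correction does not require that.
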